## Discussion

### Principal Findings

This study represents the first attempt at using the HAL for Medical Use Lower Limb Type for neurorehabilitation in individuals with lower limb amputations and also evaluates its effectiveness in early postoperative gait training. By enabling the early initiation of rehabilitation, the success rate of prosthetic gait acquisition is expected to increase. In conventional rehabilitation for individuals with lower limb amputations, active gait training is difficult during the 6-8 weeks required for residual limb maturation, leading to delays in the start of prosthetic walking. We aimed to address this issue by introducing HAL-assisted gait training from an early postoperative stage, with the expectation that it will improve the success rate of prosthetic gait acquisition, shorten the postoperative rehabilitation and hospitalization periods, enhance ADL and QOL, and contribute to medical cost reduction and efficiency. From academic and scientific perspectives, no prior reports on robotic movement therapy and neurorehabilitation based on voluntary movements in individuals with lower limb amputations exist. Consequently, this study will present the first reported findings, highlighting its academic originality and significance.

### Comparison With Prior Work

Early neurorehabilitation may facilitate the smooth acquisition of walking patterns. Previous studies on HAL-assisted gait training in patients with cerebrovascular disease have shown that repetitive, precise walking movements help maintain and improve muscle strength and balance ability [16,17]. In addition, early initiation of prosthetic gait training has been reported to enable independent walking even in older women [18]. Thus, implementing early gait training may promote recovery of physical function within the first 8 weeks of postoperative rehabilitation. Furthermore, studies have shown that patients who used a training prosthesis during rehabilitation had shorter hospital stays compared with those who did not [19,20].

### Implications for Clinical Practice and Policy

If early HAL-assisted gait training successfully enhances physical function and enables independent walking, it may lead to earlier hospital discharge and reduced medical costs. Currently, no standardized rehabilitation protocol from lower limb amputation to prosthetic gait acquisition exists [5]. If the results of this study prove effective, they may serve as a foundation for establishing a novel rehabilitation program in Japan. Moreover, HAL is currently covered by medical insurance for specific neuromuscular diseases [10], and the potential effectiveness of this study could provide scientific evidence to support the expansion of this insurance to cover individuals with lower limb amputations, potentially benefiting a broader patient population.

### Safety Considerations

Previous clinical studies have demonstrated that HAL has a favorable safety profile, with no serious adverse events reported and only minor and transient effects such as skin irritation, pressure discomfort, or fatigue [10,21]. In this study, if complications occur, specific management strategies will be applied. Skin irritation will be managed with local skin care and adjustment of electrode placement or harness fitting. Muscle fatigue will be addressed by reducing training intensity and duration or by introducing longer rest intervals. Joint pain or discomfort will lead to the temporary suspension of training followed by a medical evaluation. HAL training will only be resumed once the attending physician confirms that continuation is safe.

### Limitations

A key limitation of this study is the absence of a control group, which restricts the ability to attribute observed improvements directly to HAL-assisted rehabilitation. Moreover, the absence of a conventional rehabilitation control group limits the ability to attribute improvements solely to the HAL intervention. The single-arm design is appropriate for an exploratory investigation; however, future randomized controlled trials will be necessary to confirm efficacy and compare HAL-assisted rehabilitation with conventional rehabilitation protocols.

Second, the sample size is limited to 20 participants. This decision reflects the exploratory nature of the study and anticipates substantial individual variability in residual limb characteristics and rehabilitation backgrounds among transfemoral amputees. Third, the application of HAL is subject to technical constraints related to patient physique and residual limb condition, meaning it cannot currently be applied to all individuals with lower limb amputations. These limitations, arising from narrow eligibility criteria (eg, height, weight, and residual limb conditions), may restrict the generalizability of the findings. However, such strict criteria are necessary to ensure the safe and effective use of the HAL system, which requires specific physical and anatomical conditions for proper fitting and functionality. As the technology evolves, future studies may consider broader inclusion criteria to enhance applicability to the wider amputee population. Ultimately, this research will contribute to the development of guidelines for early rehabilitation following lower limb amputation and facilitate multicenter collaborative studies to strengthen the evidence base.

The 6-month follow-up assessment may be less sensitive in detecting differences attributable to early intervention timing; however, it is intended as a final confirmation of functional walking status. The primary outcome, however, is the 2MWD measured immediately after the 8-week intervention period, which directly reflects the effect of early HAL-assisted rehabilitation. We acknowledge that a 6-month follow-up period may not capture the full extent of functional recovery, particularly for transfemoral amputees. In particular, longer-term adaptations such as neuromuscular reorganization, prosthetic control proficiency, and reintegration into daily activities may require extended periods to fully manifest. While this duration allows for the assessment of short- to midterm effects of early intervention, the decision to limit follow-up to 6 months balances practical feasibility, participant burden, and the exploratory nature of this protocol. Future studies should consider longer follow-up periods to evaluate sustained outcomes and late-phase rehabilitation progress.

Another limitation is the strict eligibility criteria required for HAL use, including specific height, weight, and residual limb conditions. These requirements may exclude certain patient populations, which could limit the generalizability of the findings. Nevertheless, these criteria are necessary to ensure patient safety and to accommodate the technical specifications of the HAL system.

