**Figure 1 figure1:**
[figure not shown]
(Left) Hybrid Assistive Limb (developed by Japan's Tsukuba University and the robotics company Cyberdyne) and (right) walker (All-in-One, Ropox A/S).

In addition, for patients with unstable standing posture, a walker (All-in-One, Ropox A/S; Figure 1) will be used as a peripheral device for the HAL to aid walking. This walker features a battery-powered unloading lift, enabling a one-touch adjustment of the unloading weight and accommodating users of various body types and training levels. When used in combination with the HAL Lower Limb Type (NON-MEDICAL), it enables safer gait training.

The intervention outline is shown in Figure 2. An explanation of the study will be provided after an initial examination by the principal or coinvestigator. If the patient agrees to participate, they will be registered as a study participant. Before amputation surgery, preoperative assessments will be conducted, and at least one session of HAL-assisted gait training will be performed. Postoperatively, in addition to general rehabilitation exercises, HAL-assisted gait training will commence after the attending physician approves an increased activity level (mobilization clearance). HAL training will be conducted 5 days a week, with one session daily for 30 minutes. In the early postoperative phase, patients may perform HAL-assisted gait training without a prosthesis. Once the residual limb matures sufficiently and is deemed fit by the physician, a temporary prosthesis—customized for each patient but standardized in terms of structure—will be fitted to begin prosthetic-based gait training. The attending surgeon will determine the initiation of HAL training based on each patient’s postoperative recovery status, particularly the condition of the surgical wound and residual limb. If adverse skin reactions (such as inflammation, abrasions, or irritation at the electrode sites) are observed, HAL training will be suspended temporarily to avoid complications. The HAL device will be used exclusively for overground gait training during each rehabilitation session. Other tasks, such as sit-to-stand practice, orthotic fitting, and outdoor walking training, will be conducted without HAL support.

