### Outcomes

All gait evaluations at 2 weeks, 8 weeks, and 6 months postoperatively will be conducted without the use of the HAL device. For the primary outcome, assessment will be conducted at 8 weeks postoperatively to evaluate the short-term effectiveness of early HAL-assisted gait training, which is expected to influence the critical period of initial rehabilitation and prosthetic adaptation. Functional recovery may continue beyond this period, particularly up to 6 months; however, the 8-week period was chosen as the primary end point to capture the immediate impact of the intervention. A 6-month follow-up will provide important secondary data on longer-term outcomes. At each time point, walking ability will be assessed under standard conditions using the residual limb or temporary prosthesis, as applicable. A comprehensive examination of various walking-related factors is necessary; therefore, we will collect the items listed in Table 1 extensively. Among these evaluation items, the 2-minute walking distance [13,14] is set as the primary evaluation item, as it is a general indicator of walking ability and is directly linked to ADL and QOL. Other items will be collected as secondary evaluation items. The Locomo 25 is an assessment tool used to evaluate the condition of locomotive syndrome, which indicates a decline in mobility [15].

**Table 1 table1:** Primary and secondary outcomes.

Assessment item			Description

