### Statistical Analysis

The target sample size was set at 20 patients scheduled for lower limb amputation. Using JMP version 12 (SAS Institute), the sample size was calculated based on a research design assuming that the 6MWD would improve by a factor of 1.5, referencing previous studies on gait analysis using the HAL [16]. The calculation was performed with α=.05, power=0.80, and a prespecified effect size.

The primary analysis population for efficacy evaluation will be the Full Analysis Set (FAS), whereas the secondary analysis population will be the Per Protocol Set (PPS).

The FAS includes all study participants who have undergone at least one session of HAL-assisted gait training and have had at least one efficacy-related observation thereafter. However, individuals who fail to meet the eligibility criteria will be excluded. The PPS comprises participants from the FAS who have completed HAL-assisted gait training (5 days per week, 30 minutes per day) without major deviations from the study protocol and for whom the primary evaluation item can be assessed.

Statistical analyses will be conducted using SPSS version 30.0 (IBM Corp). The primary evaluation item, the 2-minute walking distance, will be analyzed using the FAS population, and the mean (SD) [or median (minimum-maximum)] will be calculated. Comparisons between preoperative, postintervention, and 6-month postoperative outcomes will be performed using a 1-way ANOVA or the Kruskal-Wallis test, with a 2-sided significance level of 5%, and a 95% CI will be calculated. In addition, the same analysis will be performed using the PPS as a secondary approach.

For secondary evaluation items, analysis will also be conducted using the FAS population. The mean (SD) [or median (minimum-maximum)] will be calculated for bilateral lower limb muscle strength, skeletal muscle mass, sensory impairment, range of motion, Berg Balance Scale, timed up and go test, gait parameters (step length, stride length, weight distribution, and gait speed during the 10-minute walk test), maximal oxygen uptake, and Locomo 25. Comparisons between preoperative, postintervention, and 6-month postoperative outcomes will be performed using a 1-way ANOVA or the Kruskal-Wallis test, and multiple comparisons will be conducted using the Tukey method (or Steel-Dwass test). A 2-sided significance level of 5% and a 95% CI will be used. The same analysis will also be performed using the PPS as a secondary approach.

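### The primary 2-minute walk comparison starts from a baseline taken before the amputation, so its P value is not evidence for or against a HAL effect, and the Limitations section contradicts itself on attribution

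*Protocol article*

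**What the plan says.** - **Baseline.** Methods, Interventions: "Before amputation surgery, preoperative assessments will be conducted, and at least one session of HAL-assisted gait training will be performed". Table 2 places physical function at preobservation, 8 weeks and 6 months.
- **Primary time point.** Methods, Outcomes: "assessment will be conducted at 8 weeks postoperatively to evaluate the short-term effectiveness of early HAL-assisted gait training". Postoperative walking is tested without HAL, on the stump or a temporary prosthesis.
- **Primary test.** Methods, Statistical Analysis: "Comparisons between preoperative, postintervention, and 6-month postoperative outcomes will be performed using a 1-way ANOVA or the Kruskal-Wallis test", two-sided at 5%, with a 95% CI. The Results section repeats this.
- **Attribution.** Limitations, on the absent control group: it "restricts the ability to attribute observed improvements directly to HAL-assisted rehabilitation". Later in the same section, on week-8 2MWD: "which directly reflects the effect of early HAL-assisted rehabilitation".
- **Population.** The inclusion criteria leave the underlying disease open. The Introduction names trauma, tumours, congenital disease and circulatory disorders as causes of amputation.
- **Sample size.** N=20 rests on a 1.5-fold gain in 6-minute walk distance (6MWD), citing reference 16, with alpha .05, power 0.8 and effect size 0.8. Comparison With Prior Work cites references 16 and 17 as "Previous studies on HAL-assisted gait training in patients with cerebrovascular disease".

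**The concern.** In most single-arm rehabilitation studies the baseline at least describes the same body before training. Here it does not. The patient has a diseased but present limb at baseline and a stump or prosthesis at week 8. A fall in distance is compatible with a useful device, and a rise is compatible with a useless one.

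The article's listed limitations cover the control group, the sample size, device and eligibility constraints, and the length of follow-up. None mentions that the baseline precedes limb loss.

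The reading of the primary result matters beyond this trial. Implications for Clinical Practice and Policy says that positive results could support wider insurance coverage, and the Conclusions section already credits early HAL training with better prosthetic walking. A P value driven by surgery and case mix could be cited for either purpose.

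**Working it through.** **1. The plan's own figure.** Inputs (Sample Size section): alpha .05, power 0.8, effect size 0.8, N=20. The type of effect size is not stated.
- Paired change, two-sided, normal approximation: n = ((1.960 + 0.842)/0.8)² = 12.3, so 13.
- The same with the t distribution: 14.3, so 15. Power at n=20 is 0.924.
- 20 is reached from 15 if 25% drop out (15/0.75 = 20), but the article gives no dropout rate.
- Three independent groups with f=0.8: 18.4 in total, so 19, or 21 if balanced.

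The figure of 20 therefore cannot be traced to one calculation. The present point does not depend on it.

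**2. What lies between baseline and week 8.** From Interventions and Outcomes: amputation, removal of the diseased part, wound and stump healing, general rehabilitation, HAL training, and possibly the start of prosthetic training. The Introduction puts stump maturation at about 6 to 8 weeks, so week 8 may fall close to first prosthetic walking. Table 2 schedules no postoperative physical-function test before week 8. The Outcomes section does mention gait evaluations at 2 weeks, but the primary comparison does not use them. Nothing planned separates the components.

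**3. What a pre-post test responds to.** Write the mean change as net = HAL effect + non-HAL change, in units of the SD of change. For a two-sided paired t-test with n=20, the critical value is 2.093 (19 df) and the noncentrality is net × √20 = net × 4.472. For net = 0.8 that is 3.578. The effects below are assumptions; the article gives none.

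| HAL effect | Non-HAL change | Net | P(significant gain) | P(significant loss) |
|---|---|---|---|---|
| 0 | +0.8 | +0.8 | 0.924 | 0.000 |
| +0.8 | 0 | +0.8 | 0.924 | 0.000 |
| +0.8 | −0.8 | 0 | 0.025 | 0.025 |
| +0.8 | −1.6 | −0.8 | 0.000 | 0.924 |
| 0 | −0.8 | −0.8 | 0.000 | 0.924 |

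The first two rows give the same result with and without a HAL effect, and so do the last two. Only the net counts.

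**4. The planned test.** The paired test is a simplification. The article plans an omnibus test over three time points, with the preoperative value as one of them. That test has no direction, so a clear loss also gives P<.05, and the 6-month value can drive the result.

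**5. The planning gain.** The 1.5-fold figure cites reference 16. The article elsewhere places references 16 and 17 in cerebrovascular disease. No section gives a reason to expect that gain from before to after an amputation. Without a baseline 2MWD, an SD, a within-patient correlation or an expected change across amputation, no replacement N can be computed.

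**The case against.** - **The missing control is already conceded.** The Limitations section says so twice, calls the study exploratory and asks for randomised trials. This stands: general rehabilitation and natural recovery are covered by that concession. The pre-amputation baseline is not.
- **The disputed sentence explains the choice of week 8 over 6 months.** It can be read as describing closeness to the intervention, and it governs no analysis. That is a fair reading of its purpose, but the words make a causal claim about the primary outcome that the same section withdraws.
- **HAL training starts before surgery, so only a preoperative measurement can precede it.** True. Taking the baseline then is understandable; the difficulty is what the comparison is said to show.
- **Week-8 2MWD is already the primary outcome, with a mean and 95% CI planned.** Also true, which makes the remedy small.

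Some stronger readings are not supported. A reader might infer that the 1.5-fold assumption is wrong for amputees. The documents show only that no basis is stated: reference 16 is not available here, and the net change could go either way. A reader might also infer that patients will be scored as a ratio to their baseline, which would fail for non-walkers. No such endpoint is planned; distances are analysed as means or medians. Nor can an SD of change be derived from the 1.5-fold gain and the 0.8, since the article does not say that they describe the same paired quantity.

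**Conclusion.** The concern holds in this form. The omnibus P value for 2MWD, significant or not, is not evidence for or against a HAL effect. The Limitations section contradicts itself on attribution and omits the pre-amputation baseline. The planning gain is unsupported for this setting.

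The real size of the non-HAL change is unknown. The probabilities of 0.92 and 0.025 rest on assumed effects of 0.8 SD, complete data on 20 patients and a paired test in place of the omnibus test. They show that the result can go either way, not how likely either is.

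A reader might infer that the trial is worthless or that it needs an external comparator. Neither follows. The week-8 and 6-month distances remain usable as descriptive estimates, and the article presents the study as exploratory. What should change is the stated interpretation.

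**What to change.** 1. Limitations: replace the statement that week-8 2MWD directly shows the HAL effect with wording that agrees with the concession about the control group.
2. Statistical Analysis and Results: state that the comparison with the preoperative value is descriptive and will not be interpreted as evidence of HAL efficacy. Make the week-8 2MWD estimate with its 95% CI the primary readout.
3. Limitations: add that the baseline precedes the amputation and that later tests are made on the stump or a prosthesis.
4. Sample Size: either justify the 1.5-fold gain and effect size 0.8 for a change across an amputation, or describe N=20 as based on feasibility or precision. For precision, 20 complete patients give a 95% CI half-width of 2.093/√20 = 2.093/4.472 = 0.47 of the between-patient SD of week-8 2MWD. The article gives no value for that SD.

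The cost is text only; design, visits and data collection are unchanged. The downside is a more modest claim.

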### Conclusions

Early postoperative HAL-assisted gait training can increase the success rate of prosthetic walking, shorten the rehabilitation period, and reduce medical costs. The findings of this study are expected to contribute to the establishment of a standardized rehabilitation program originating from Japan for individuals with lower limb amputations and also serve as a foundation for novel clinical applications of HAL.

## Abbreviations

2MWD: 2-minute walk distance
6MWD: 6-minute walk distance
ADL: activities of daily living
BI: Barthel Index
FAI: Frenchay Activities Index
FAS: Full Analysis Set
FIM: Functional Independence Measure
HAL: Hybrid Assistive Limb
PPS: Per Protocol Set
QOL: quality of life
SPIRIT: Standard Protocol Items: Recommendations for Interventional Trials
